#### Study procedure

Figure 1 provides an overview of the pilot trial design. The two MCH clinics that we build capacity in Aim 2 will be the pilot Implementation sites. During the 1st implementation cycle (about 2–3 months), we will work with only 1 MCH clinic (Cohort 1), and then work with another MCH clinic in the 2nd implementation (Cohort 2). For each cohort, 45 pregnant adolescents with moderate to severe depression will be recruited. As the interventions will be using self-reported measures and the adolescent participants would be directly involved the intervention arms would be unmasked.

#### Inclusion criteria (for the implementation feasibility and impact estimate study)

Pregnant adolescents (ages 13–18), screened with moderate to severe depression during the 1st to 2nd trimester (defined as Edinburgh Postnatal Depression Screen (EPDS) score ≥ 13 or meet the APA’s Diagnostic and Statistical Manual for Mental Disorders IV-TR version (DSM-IV-TR) criteria for major depression disorder and perinatal depression), who agree to give informed consent (by adolescents and their adult caregivers), are willing to come for group sessions at MCH clinic, can participate in evaluation assessment and give consent to publish the findings of the work, will be eligible. Participants will be excluded from the study if they suffered from or showed evidence of severe personality disorder, acute psychosis, suicidality, (however will be given referral to appropriate services upon identification of any significant risk) or where there will be significant substance abuse, or evidence of severe comorbidities.

#### Intervention implementation

Participants will be randomly assigned to IPT-G Full, IPT-G Mini, and wait-list control using computer random generator by research staff (*n* = 15 for each arm, 45 per cohort).
The IPT-G Full and Mini groups will receive the assigned interventions (8 vs. 4 sessions) developed from Aims 1 and 2 (including a perinatal depression educational material/handout). To avoid contamination, intervention for the IPT-G Full and Mini versions will be carried out by 2 separate implementation teams (2–3 facilitators in each team) follow the assigned manual/protocol. Figure 2 provides intervention contents for the Mini version, in comparison to the recommended Full version.The Control will receive standard care (with referral) and perinatal depression educational materials for safety concerns. They will receive IPT-G Mini after the post implementation assessment is completed.

**Fig. 2 Fig2:**
[figure not shown]
Schedule of Enrolment, Interventions, and Assessments.**Recommended content can be displayed using various schematic formats. See SPIRIT 2013 Explanation and Elaboration for examples from protocols

#### Feasibility evaluation measures and procedure

To evaluate feasibility of the mhGAP-IG/IPT-G implementation model in the MCHs, a mixed methods data collection approach will be applied and data will be collected from multiple sources (i.e., implementers, MCH leaders, adolescent mothers and their family members) to minimize data collection bias. As described above, the *Conceptual model of Implementation Outcomes* [56] is applied to guide the construct selection for the implementation feasibility and impact estimation. Feasibility of the mhGAP/IPT-G mental health service delivery model will be assessed using three indicators: fidelity (i.e., % of sessions is delivered with > 80% of contents), level of engagement (e.g., % reach targeted population, % participating in intervention sessions), quality of implementation (e.g., acceptability, appropriateness, usefulness, satisfaction of the mhGAP/IPT-G service model), and perceived mental health service (e.g., mental health service quality, MCH climate). Feasibility of applying a trial design for mhGAP/IPT-G impact evaluation in MCHs will be assessed using two indicators: % of adolescent-caregiver pairs that are exposed to intervention contents within the assigned condition; and % of data collection performed as planned. Impacts/effect size estimation for the IPT-G Full and Mini versions (the secondary outcomes) will be assessed for adolescents’ mental health and family functioning outcomes. Both quantitative data and qualitative data will be collected. Qualitative data will be collected through focus groups (2 groups for each intervention arm) at the end of implementation cycle. Tables 1 and 4 lists the feasibility outcomes measures and sources of data collection (under implementation feasibility, mental health service outcomes, and trial design feasibility and effect size estimation). Implementation feasibility outcome data, collected from the MCH staff/intervention implementers and adolescents who participated in the two intervention arms (IPT-G Full and Mini), will be gathered after each group session throughout the two implementation periods. For effect-size estimation, all study participants will complete a baseline (Time 1) interview (on mental health and family functioning outcomes) before randomization and intervention implementation, followed by a 1- or 2-month implementation period (2 months for the IPT-G Full and 1 month for the IPT-G Mini). Only when a participant is physically unwell, or has to terminate due to a pregnancy related emergency or any other severe mental health issue will their participant grouping be unblinded and an appropriate referral made. They will receive a post-intervention interview assessment at the end of implementation cycle (Time 2, about 3–4 months after the Time 1). To facilitate coordination of program implementation activities, participating MCH will be provided with two tablets and a small incentive which could offset implementation costs.

**Table 4 Tab4:** Research implementation steps and data gathering activities

**Research Implementation steps and data gathering activities**	Protocol development, pre-testing of tools and training; formation of technical and community advisory boards	Mixed qualitative methods inquiry on facilitators and barriers to uptake of evidence- based interventions for depression care in primary care settings for pregnant adolescents	Adaptation of mhGAP depression care guidelines and treatment intervention for pregnant adolescents	Observational notes for clinical workflow in primary care and training in integrated mhGAP and IPT-G for depression care	Adaptation of brief IPT-G	Test feasibility of implementation and estimate the size of effect on mental health for the adapted version of mhGAP-IG/ IPT-G.	Analyses, writing and dissemination
**Sample**	Community advisory (17members), Technical advisory board (5 members)	40 participants (8 FGDs with 5 members per group),	Utilizing community advisory and technical advisory boards for adaptation process; expert consultation as and where needed	20 researchers and 16 providers	Utilizing community advisory and technical advisory boards for adaptation process; expert consultation as and where needed	90 pregnant adolescents in a three-arm study: IPT-G Full and IPT-G Mini	Compiling all the information derived from all participants and consultations with mentors, experts and advisory board members
**Location of activity**	In person and virtual meetings with study team members and mentors	Community and health facility based	Desk-based activity including expert consultation with partners from Department of Psychiatry University of Nairobi, Department of Mental Health MoH, WHO, UNFPA and Nairobi county	Community and health facility sample	Community and health facility sample	Community and health facility -based purposive sampling	Virtual, in-person one-on-one and group discussions and meetings with research team, advisory board members and mentors
**Training of health workers and capacity building activities**	Train two-four career researchers, engage communities and build networks with Ministry of Health, mapping a referrals process for any medical or psychosocial issue arising during study	Train data collectors & RAs in two sites, train teams in psychological first aid, identify community health workers for linkages in case of any referrals for those with high depression or at risk for mental or physical	Collaborative work with the research team; three early career researchers and postgraduate students trained in mhGAP and IPT-G; technical and community advisory	Collaborative work with research team, trained researchers to train health facility workers and community health workers; capacity building of the health facility nurses in depression screening for adolescents especially peripartum	Collaborative work with the research team; trained health facility and community providers; technical and community advisory and mentors	Trained data collectors from Aim 1 would be re-engaged and additional trainings and capacity building on survey data collection will be carried out before the survey is collected. Quality assurance checks will be carried out after first 5 participant survey data per site and training repeated if there are discrepancies	Dissemination of findings to Ministry of Health and Nairobi County, Training programs for health facility workers with county and ministry of health using mhGAP
**Data collection method**	Iteratively developed mixed methods inquiry with expert consultation, community advisory support	a. FGDs, KIIs b. Short survey for conjoint experiment	a. Stakeholder engagement through advisory board meetings and group discussions, b. Expert feedback	a. ethnographic- observational study, b. training workshops with the researchers, c. training workshops in the health facilities	a. Stakeholder engagement through advisory board meetings and group discussions, b. Expert feedback	feasibility trial with individual level randomization- Intervention will be delivered in groups at the health facility and data would be collected during each session and after session	Mixed methods analysis: psychometrics/multivariate analyses/ mixed qual methods
**Domains addressed /focal activities**	Comprehensive community based participatory approach integrating strengths and needs of key partners from Ministry of Health, Nairobi County, WHO and UNFPA	Depression care needs from multiple stakeholders; depression care treatment preferences	Adaptations and modifications for WHO mhGAP depression treatment manual and IPT-G manual for peripartum adolescents	Integrated work-flow plan to address mental health needs of pregnant adolescents	Brief version of IPT-G which has been validated for use by technical and community advisory	Multilevel assessments from participants, providers and facility managers on acceptability, appropriateness, and usefulness of the adapted version and implementation process of the mhGAP-IG/ IPT-G service model; and adolescent self- report depression and functioning outcomes;	Several planned publications including: a. mhGAP/IPT-G adaptation for adolescent mothers with depression; b. Acceptability and Appropriateness of the Brief and Long versions of IPT-G intervention implemented by CHWs (results from a mixed method study), c. D&I context measures validation paper, d. Implementation Effectiveness Evaluation (using RCT implementation study data to study effectiveness for brief and long version of IPT-G)
**Outcome measure/s or final output**	Finalized protocol with all IRB clearances and peer reviewed by a wide group of specialists	Multi-stakeholder appraisal of depression care treatment preferences	Integrated mhGAP depression care with modified IPT-G manual	New workflow plan to organize clinical services around mental health care for pregnant adolescents	Finalized version of the manual	Acceptable and useful integrated mhGAP depression care and modified IPT-G for adolescents, health facility and community health workers. Evidence of small to moderate size of intervention effect on adolescents. See Tables 1 and 2	Peer reviewed publications, conference presentations, dissemination in the three communities through Ministry of Health and in the scientific community

#### Sample size

A randomly selected sample of 90 adolescent-parent dyads will be recruited. It has been suggested that a minimum of 30 participants per group/arm is sufficient for individual IPT and IPT-G pilot studies based on similar intervention studies in LMICs [17, 18, 23].

#### Analysis plan for the feasibility outcomes

Data collected through 2 cohorts will be analyzed. Quantitative analysis will be focused on examining the following questions:
Examine acceptability, appropriateness, usefulness, engagement, and fidelity for both full and mini versions of integrated mhGAP/IPT-G intervention implementation using task-shifting/sharing approach in MCH contexts.Examine MCH service quality change patterns before and after implementation of the mhGAP/IPT-G model will improve.Examine whether pregnant adolescents in the IPT-G will have better outcomes relative to control, but high impacts/effect size for the IPT-G Full version.

The following stop-go criteria will be used to determine whether to proceed to the main trial: the recruitment proceeds well so that the first IPT-G cohort can proceed by the end of the first month of the specified recruitment period. The IPT therapists that is the trained CHVs and nurses demonstrate adequate levels of treatment fidelity to the WHO IPT-G checklist adherence available in the manual and 70% of participants attend at least 5 of the available sessions in the course of their treatment and 80% are successfully followed up at primary endpoint.

Quantitative analysis for *implementation outcomes* will be based on data collected throughout the implementation period, and analyzed separately for each time point as well as jointly to create overall summary scores. Analysis for the *MCH service outcomes* will be based on pre-post intervention data using *paired-t tests* and repeated measures. We will examine patterns separately and jointly for two MCH clinics. Analysis for *estimating size of impact* on mental health (depression) and family functioning will be based on multi-level modeling, adjusting for family/group nesting effects. Post-intervention effects/impacts will be estimated as a function of baseline levels of the corresponding outcome variables and intervention status. Effect size (regardless the statistical testing significant level) will be computed. *Quantitative data* for implementation outcomes, MCH service outcomes, and adolescent mental health effectiveness outcomes will be examined separately.

*Qualitative data* will be transcribed and analyzed using similar techniques described in Aim 1. We will review all focus group discussion data and use grounded theory approach to search for emerging themes using open and axial coding. Analysis will focus on themes related to MCH service quality (on providing both MCH and mental health care), feedback on implementation process and intervention contents, and perspectives on theory of change.

### Methodology for sub-study 1

To understand ‘fit’ of the mhGAP/IPT-G and study barriers/strategies (in 5 CFIR domains) to promote utilization and impacts of mhGAP/IPT-G, we will carry out a mixed methods study, including qualitative and quantitative data collection. Quantitative data collection will focus on D&I readiness contexts and new D&I tools pilot testing (see Table 4 and Fig. 3 for data gathering activities for the entire study and SPIRIT chart).

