### Methodology for primary pilot trial

Considering high prevalence of adolescent pregnancy, high risk for depression in this population, and low resource in MCH clinics, the WHO recommended Full version of IPT-G may not be practical in meeting population service demands and needs. Therefore, we will test a Mini version of IPT-G in comparing to the Full version of IPT-G in the context of mhGAP mental health service delivery model. For this Aim, our primary goal is to evaluate the feasibility of implementing the integrated mhGAP-IG/IPT-G service model in the MCH contexts as well as feasibility of applying RCT design to study differential impacts of the IPT-G Full and Mini version in MCHs. Our secondary goal is to estimate the sizes of effect for the mhGAP/IPT-G Full and Mini versions.

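### The stop-go rule gives one verdict without naming a version, so it has no output if IPT-G Full fails and Mini passes, and its attendance bar does not fit the 4-session Mini arm

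*Protocol article*

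**What the plan says.** All references are to the protocol article.

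- **Reason for Mini** (Methodology for primary pilot trial): "the WHO recommended Full version of IPT-G may not be practical in meeting population service demands and needs". The Mini version is introduced as the response to this.
- **Delivery** (Intervention implementation): "The IPT-G Full and Mini groups will receive the assigned interventions (8 vs. 4 sessions"). Separate teams deliver the two versions, each to its own manual. Each arm has 15 adolescents per cohort, and the wait-list control is offered Mini after the post-implementation assessment.
- **Planned examination** (Analysis plan for the feasibility outcomes): the first question covers "engagement, and fidelity for both full and mini versions of integrated mhGAP/IPT-G intervention implementation".
- **Decision rule** (same section): "The following stop-go criteria will be used to determine whether to proceed to the main trial". Four criteria follow:
  - recruitment such that "the first IPT-G cohort can proceed by the end of the first month of the specified recruitment period";
  - therapists who "demonstrate adequate levels of treatment fidelity to the WHO IPT-G checklist adherence available in the manual";
  - attendance: "70% of participants attend at least 5 of the available sessions in the course of their treatment";
  - follow-up: "80% are successfully followed up at primary endpoint".

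No criterion names Full or Mini, the attendance criterion names no denominator, and no outcome is given in which one version proceeds without the other.

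**The concern.** The rationale treats it as possible that Full will not be practical in these clinics while a shorter version will be. A progression rule should have an answer for that result, and this one has only go or stop for a single main trial. If the criteria are pooled over versions, a weak version can be masked by a strong one, or can pull it down. If every version must pass, failure of Full also stops Mini. Either way, the feasibility results collected for each version do not determine what goes forward.

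The attendance criterion adds a second problem. It counts sessions on a scale that fits the 8-session version but exceeds what the 4-session version offers. Splitting the rule by version would therefore not help Mini unless the session count is reconciled too.

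**Working it through.** **Sample size.** 15 per arm × 3 arms × 2 cohorts = 90, which reproduces the stated total. That is 30 per arm, and 60 in Full and Mini together.

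**The attendance criterion as written.** The bar is at least 5 sessions attended by 70% of participants. Full offers 8 sessions and Mini 4, so no Mini participant can qualify. With perfect attendance:

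| Denominator | Needed for 70% | Most that can qualify |
|---|---|---|
| Full only | 21/30 | 30/30 = 100% |
| Mini only | 21/30 | 0/30 = 0% |
| Full + Mini | 42/60 | 30/60 = 50% |
| All randomised (control gets Mini later) | 63/90 | 30/90 = 33.3% |

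Pooled, the rule can only stop. By version, it can only ever pass Full.

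**The single verdict once the bar is attainable (illustration only).** Assume a bar that both versions can reach, 30 adolescents per version, the 70% threshold and independent attendance. The article gives no attendance rates, so the rates below are assumptions.

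- By version: P(pass) = P(X ≥ 21), with X ~ Binomial(30, p). P(only Mini passes) = P(Mini passes) × [1 − P(Full passes)].
- Pooled: P(go) = P(X_Full + X_Mini ≥ 42), from the exact sum of the two binomials.

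| Assumed Full / Mini | P(Full passes) | P(Mini passes) | P(only Mini passes) | P(pooled go) |
|---|---|---|---|---|
| 50% / 90% | 0.02 | 1.00 | 0.98 | 0.57 |
| 55% / 85% | 0.07 | 0.99 | 0.92 | 0.57 |
| 50% / 85% | 0.02 | 0.99 | 0.97 | 0.39 |
| 60% / 80% | 0.18 | 0.94 | 0.77 | 0.56 |

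So where results by version would usually point to Mini alone, a pooled rule says go for both with probability 0.39 to 0.57 and otherwise stops both. A rule that required both versions to pass would stop whenever only Mini passed.

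**Cost of judging by version.**

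- Exact (Clopper-Pearson) 95% interval at an observed 70%: 21/30 gives 50.6-85.3%; 42/60 gives 56.8-81.2%.
- At an assumed true attendance of 75%: P(X ≥ 21 of 30) = 0.80; P(X ≥ 42 of 60) = 0.85.

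**The case against.** **A single gate can be legitimate.** The stated primary goal is feasibility of the service model and of a randomised design, and effect sizes for the two versions are secondary. A main trial comparing Full with Mini would need both, and its design is not given. This stands against a reading that a reader might adopt, namely that the study was set up to find a go for Mini alone. No section names that as the target, and the analysis plan itself anticipates larger effects for Full. It does not remove the gap: if both versions are to go forward together or not at all, the rule should say so.

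**Evidence by version is planned.** Feasibility data are collected after each session in both intervention arms, focus groups are held per arm, and a paper on the acceptability of the brief and long versions is listed. This also stands. It would be wrong to infer that the pilot cannot show which version fits the clinics. Only the link from that evidence to the decision is absent.

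**The masking scenario is hypothetical.** Under the written bar a pooled go cannot occur, because at most 50% can qualify. A reader might infer that the present rule would carry an infeasible Full arm into the main trial on the pooled figure; the text does not allow that. Pooling is itself only one reading. The probabilities above show what would remain after the session count alone was corrected.

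**The article is condensed.** Detail may sit in a fuller document. But the article states the rule, and both the rule's single verdict and the conflict between its attendance bar and the Mini session number are in the text.

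**Conclusion.** The point holds in a limited form. The fidelity and attendance criteria are stated once, without version or denominator, and give one verdict. The rule therefore has no output for the case that the rationale raises, and the planned examination by version does not feed into it.

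The attendance bar is also inconsistent with the 4-session arm. This part follows from the article's own figures and needs no assumed rates: at most 50% pooled over Full and Mini, and 0/30 for Mini, against 70% required.

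The size of the single-verdict problem, once the bar is attainable, depends on assumed attendance. Over the four pairs tried, only Mini passes with probability 0.77 to 0.98, while a pooled rule says go with probability 0.39 to 0.57. The two defects need correcting together, since neither correction is enough alone.

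**What to change.** Amend the stop-go paragraph and reconcile it with Intervention implementation:

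1. Reconcile the session count in the two sections, so that the attendance criterion is defined relative to the sessions offered in each version, and name its denominator. The investigators must decide what counts as adequate attendance.
2. Apply the fidelity and attendance criteria to IPT-G Full and IPT-G Mini separately.
3. Keep recruitment and follow-up as trial-level criteria.
4. State the progression result for each version, including what follows if only one meets its criteria. If the main trial is to keep both versions regardless, say that.

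No new data are needed, because implementation data are already gathered after each session in both arms and the versions have separate teams. The cost is precision. Each version is judged on 30 rather than 60 adolescents, and at an assumed true attendance of 75% a version would miss the 70% bar about one time in five (1 − 0.80 = 0.20), against 0.15 pooled.

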### Design overview and setting of the study

A rigorous mixed methods study will be used to study strategies to adapt and improve mhGAP-IG and IPT-G for Kenyan adolescent population and MCH implementation contexts. The pilot implementation study will be based at two Nairobi primary health care centers—Kariobangi North and Kangemi. Kariobangi is a low-income residential estate in north eastern part of Nairobi, Kenya. Kariobangi consists of both lower middle class and slum-type dwellings and is split into two parts: Kariobangi North and Kariobangi South. Kariobangi North is located approximately 15 kms from Nairobi city center. Kariobangi north is estimated to have 8000 to 10,000 residents. Kangemi is a slum in Nairobi County located in a small valley on the outskirts of the city. It is bordered on the north by the middle-class neighborhoods of Loresho and Kibagare and Westlands on its west. Different sources report that Kangemi has more than 100,000 residents. The study will be conducted in Nairobi at the Nairobi County’s two primary health care facilities that offer MCH services. The study is conducted in collaboration among partners from the University of Nairobi, Ministry of Health (Community Health Promotion and Mental Health Departments), WHO non-communicable diseases unit, and UNFPA’s adolescent SRH section. After enrolment, adolescents will be followed through regular clinic visits in the two respective centers. The study clinic will have dedicated staff including clinical and nursing officers able to provide clinical care offered as part of routine Antenatal Clinic (ANC) care for pregnant adolescents. The assumption is that the pregnant adolescent will seek the intervention and ANC at the clinic site from where she was recruited. The delivery options might vary depending on the personal situation, obstetric history and medical complications associated with pregnancy. However, the participants will be tracked on the delivery and birth outcomes wherever childbirth takes place.

Kenyatta National Hospital/University of Nairobi ethics review committee has approved the study and additional approvals were sought from Nairobi county health directorate and National Commission for Science, Technology and Innovation which will be renewed annually (as per the respective committee policies).

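### The stop-go rule tests recruitment only by the start of the first cohort, so the number recruited at the second clinic has no effect of its own on the decision to proceed

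*Protocol article*

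**What the plan says.** All references are to the protocol article. Under Analysis plan for the feasibility outcomes, the decision rule is introduced with "The following stop-go criteria will be used to determine whether to proceed to the main trial". Four conditions follow:

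- Recruitment: "the recruitment proceeds well so that the first IPT-G cohort can proceed by the end of the first month of the specified recruitment period".
- Fidelity: the trained therapists "demonstrate adequate levels of treatment fidelity to the WHO IPT-G checklist adherence available in the manual".
- Attendance: "70% of participants attend at least 5 of the available sessions in the course of their treatment".
- Follow-up: 80% followed up at the primary endpoint.

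The Study procedure section says that in the first cycle "we will work with only 1 MCH clinic (Cohort 1), and then work with another MCH clinic in the 2nd implementation (Cohort 2", with 45 adolescents to be recruited for each cohort. Intervention implementation gives 15 per arm in each cohort. The Sample size section plans 90 dyads, on the ground that "a minimum of 30 participants per group/arm is sufficient" for pilots of this kind.

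Two related items lie outside the stop-go list. Table 1 sets, as a success criterion for the feasibility of the RCT method, that 80% of data collection is carried out as planned. Feasibility evaluation measures and procedure lists the percentage of the target population reached as an engagement indicator, with no threshold.

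**The concern.** Methodology for primary pilot trial makes it part of the primary goal to learn whether an RCT can be run in maternal and child health clinics. Whether enough depressed pregnant adolescents can be recruited at each clinic is central to that question. The two clinics recruit in sequence, so an on-time start at the first gives no count for the second.

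The rule looks at recruitment once, at one clinic, at the start, and without a number. The remaining conditions describe how enrolled participants and their therapists behave. A pilot that recruits poorly at its second site could therefore still be judged ready for the main trial. This is a property of a rule that the article states in full, not a detail left for a later document.

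**Working it through.** **Planned numbers.** 2 cohorts × 3 arms × 15 = 90, and 3 arms × 30 = 90. The planned total and the 30 per arm agree.

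**The rule as written.** Proceed if the first cohort starts by the end of month 1, fidelity is adequate, at least 70% of participants attend 5 or more sessions, and at least 80% are followed up. Neither second-cohort enrolment, nor the total of 90, nor the 30 per arm enters any condition.

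**Evaluating it for different second-clinic enrolments.** Illustrative assumptions, not in the document: the first cohort starts on time, fidelity is adequate, about 80% attend (counted in the Full arm only, for the reason given below), and 90% are followed up, rounded up to whole persons.

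| Recruited at second clinic | Total (of 90) | Per arm | Full-arm attendance | Follow-up among enrolled | Rule | Follow-up against planned 90 |
|---|---|---|---|---|---|---|
| 0 | 45 (50%) | 15 | 12/15 = 80% | 41/45 = 91% | proceed | 41/90 = 46% |
| 15 | 60 (67%) | 20 | 16/20 = 80% | 54/60 = 90% | proceed | 54/90 = 60% |
| 30 | 75 (83%) | 25 | 20/25 = 80% | 68/75 = 91% | proceed | 68/90 = 76% |
| 45 | 90 (100%) | 30 | 24/30 = 80% | 81/90 = 90% | proceed | 81/90 = 90% |

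**Does a smaller sample make the follow-up condition fail?** Assume a true follow-up probability of 85%. The binomial probability of observing at least 80% is 0.93 for N = 90 (at least 72), 0.89 for N = 60 (at least 48) and 0.87 for N = 45 (at least 36). Halving the sample barely changes the chance of passing.

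**What if 80% were counted against the planned 90?** Then 0.80 × 90 = 72 would have to be followed up. With 45 from the first clinic, the second would have to supply at least 72 − 45 = 27, even with complete follow-up. On that reading the second clinic's head-count would matter. Neither the follow-up condition nor Table 1 states this denominator.

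**Can second-clinic data change the decision at all?** Yes, through the percentages. If 41 of 45 are followed up at the first clinic and 30 of 45 at the second, the total is 71/90 = 79%, which fails. What has no effect of its own is the number recruited.

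**Attendance.** The Full version has 8 sessions and the Mini version 4, so no Mini participant can attend 5. Pooling the two equal arms, at most 15/30 = 50% can meet the condition, and 70% is out of reach at any enrolment. A decision to proceed is possible only if attendance is read for the Full arm alone, which the text does not say.

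**The case against.** The strongest reply is that Table 1 already covers the RCT-feasibility question. If its 80% of planned data collection is taken against 90, a pilot with 45 or 60 participants reaches at most 50% or 67% and fails. That is a reasonable reading and limits the concern. However, the criterion has no stated denominator and is not among the conditions said to decide progression. The annual report on progress toward recruitment goals (Study dissemination plans) and the reach indicator carry no threshold either.

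Several stronger inferences are tempting, and the document does not support them:

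- A reader might infer that a pilot failing at its second clinic meets every condition to proceed. That holds only if the other three conditions pass. Second-clinic participants can move those percentages, and the attendance condition cannot be met at all if Full and Mini are pooled.
- A reader might infer from "Kariobangi north is estimated to have 8000 to 10,000 residents" and "Kangemi has more than 100,000 residents" that the clinics' recruitment potential differs about tenfold. These are area populations, not clinic catchments. The Background gives 20–30 pregnant adolescents per week in each Nairobi clinic. The article also does not say which clinic goes first.
- A reader might measure the harm by the lost precision of effect estimates, or treat 30 per arm as a progression threshold. Effect sizes are a secondary goal, and the 30 is a sample-size rationale. It serves here only to show how far the pilot could fall below its own plan.

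A team may choose an early-start milestone plus quality thresholds. That defence has some force, but it leaves recruitment at half the planned sample outside the decision.

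**Conclusion.** The point stands in a limited form. The stop-go rule's only recruitment condition is the timely start of one of two clinics. Provided the fidelity, attendance and follow-up conditions pass, with percentages taken over those enrolled, any second-clinic enrolment from 0 to 45 leads to the same decision. At the extreme the pilot has 45 of 90 participants and 15 per arm, half of what was planned. The conclusion would change only if the follow-up condition, or a Table 1 criterion brought into the rule, were counted against the planned 90.

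This should be corrected, because the stated rule can return an unwarranted decision to proceed on the pilot's primary question, and because the counts needed to prevent it will be available anyway.

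**What to change.** Keep the month-1 start as a progress check. Add to the stop-go rule a numeric recruitment criterion covering both cohorts, set before results are seen. One example uses the protocol's own 80% level: 0.80 × 45 = 36, so at least 36 of the planned 45 randomised in each clinic within that cohort's recruitment period, and at least 72 of 90 in total. The minimum of 72 gives 72/3 = 24 per arm, so the team should state that it accepts this shortfall from 30 or choose a higher level.

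State that Table 1's 80% data-collection criterion is counted against the planned 90. Counted that way it is the stricter of the two: 72 recruits would need complete data collection, and at 90% completion 72/0.90 = 80 recruits would be needed. Report recruits per clinic with the decision.

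Separately, the 5-session attendance condition and the 4-session Mini arm must be reconciled.

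The cost is protocol wording, with no new data collection. A decision to proceed becomes somewhat harder to reach and cannot be declared on recruitment until the second cohort closes.
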